#### Interim analyses

Interim analyses will be performed to evaluate achievement of the primary objective of the study. The analyses will be conducted twice during the study. Participant recruitment will be continued during the interim analyses.

For the interim analysis, the Lan-DeMets spending function will be used to adjust for multiplicity and to maintain the alpha error of the overall study at 2.5% for the one-sided test. The difference between the two groups in the period up to the event occurrence, using the O'Brien-Fleming alpha-spending function, will be examined for statistical significance.

The study will be terminated if the period up to the event occurrence in the trial intervention group exceeds that of the control group and the *p*-value of the log-rank sum test is less than the significance level defined by the method described above.

#### Secondary analysis

Secondary outcomes will be examined in order to reinforce the findings of the primary analysis. For analysis of secondary outcomes, the period up to event occurrence will be analyzed with the stratified log-rank test. Subgroup analysis of the primary and secondary outcomes will be performed by hospital, gender, age (< 40 or ≥ 40 years), and occurrence of suicide attempt before enrollment in this study. Because of the exploratory nature of the secondary analysis, no adjustment for multiplicity will be made.

### Ethical considerations

In this study, the rights and welfare of the participants will be protected according to the World Medical Association Declaration of Helsinki: Ethical Principles for Medical Research Involving Human Subjects. The study will comply with the ethical guidelines of the Ministry of Health, Labour, and Welfare in Japan. Ethical validity, including safety, scientific legitimacy, and reliability of results are ensured. Personal information collected by the participating hospitals in this study will include no identifiers that could be used to determine the identity of an individual and, therefore, will be made anonymous.

### Study monitoring

#### Periodic monitoring

The data management center will submit a monitoring report, including the information listed below, to the J-MISP administration office once every 3 months. The J-MISP administration office will send the monitoring reports to the study progress control committee, the Central Research Ethics Committee, and the study group management office.

The study progress control committee will examine the periodic monitoring reports and submit the evaluation to the J-MISP director. As a third party, the central research ethics committee will evaluate the periodic monitoring reports and make recommendations to the J-MISP director to revise the study protocol or stop the study, if ethical problems, such as safety and efficacy issues, should arise.

#### Contents of monitoring reports

1) Progress of the study, including enrollment

2) Status of the implementation of psychiatric evaluations

3) Data on the occurrence of events (according to the blinded group allocations)

4) Data on the occurrence of adverse events (according to the blinded group allocations)

5) Other relevant information, such as presence of undesirable issues and/or events

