## Methods/Design

ACTION-J is an open, randomized, controlled, multicenter study which examines the effectiveness of a trial intervention for suicide attempters in Japan. The trial intervention involves the implementation of case management for suicide attempters transported and admitted to emergency medical facilities. The task schedule is presented in Table 1.

**Table 1 T1:** Task schedule

	**during admission**	**at discharge**	**1 w after discharge**	**4 w**	**8 w**	**12 w**	**6 m**	**12 m**	**18 m**	**24 m**	**30 m**	**36 m**	**42 m**	**Interim/Final analysis**
Psychiatric diagnosis	◎													
Psychoeducation 1*	◎													
Informed consent	◎													
Enrollment/randomization	◎													
Input data at time of discharge		◎												
Case management (Psychodeucation 2**, others)	○		○	○	○	○	○	○	○	○	○	○	○	
Psychiatric evaluation	◎						◎		◎		◎		◎	
Event	Input content of the event (ie, recurrent suicidal behavior, adverse event) into the web system as occasions require													
Participant survival (or cause of death of the participant)														◎
Actions to critical situations	In both groups during the study as occasions require													
Reports of a serious adverse event	Prompt report to the director of the hospital and the study group management office in both groups as occasions require													

◎: implemented in both groups; ○: implemented only in experimental intervention group

*: Psychoeducation Program I to all participants in both groups

**: Psychoeducation Program II to their family members during hospitalization in the experimental group

w: week, m: month

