#### Events

Events will be classified as follows:

1) Recurrent suicidal behavior

2) Total deaths (from any cause)

3) Self-harm

4) Adverse events other than (1), (2), or (3): Any unfavorable and unintended occurrence in a participant, whether or not there is a causal relationship with the intervention, will be recorded.

When identifying an event, the on-site research staff at the participating hospital will record the information according to the event review sheet and will confirm the information with the investigator. If there are no complications, the on-site research staff will enter the content of the event into the web input system. If necessary, on-site research staff will consult with the on-site research coordinator and the study group management office regarding any aspects of the event that are unclear. The on-site research coordinator will notify the hospital director about any serious adverse event and will fax the event review sheet directly to the study group management office.

The data center will consolidate the input data and periodically provide data to the study group management office and the chairperson of the event review committee, according to data management procedures. The study group management office and the chairperson of the event review committee should hold monthly event review meetings to evaluate and assess details of events based on the material provided.

Specific aspects of events will be described in the event definitions and event review procedures.

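### Quarterly event data, most naturally read as split by coded group, go to the office that runs this open trial, and the reports may support an efficacy stop that has no boundary

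*Protocol article*

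**What the plan says.** All references are to the Protocol article.

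- **Design.** Methods/Design states: "ACTION-J is an open, randomized, controlled, multicenter study".
- **Frequency.** Under Periodic monitoring, the data management center reports "to the J-MISP administration office once every 3 months".
- **Recipients.** That administration office "will send the monitoring reports to the study progress control committee, the Central Research Ethics Committee, and the study group management office".
- **Content.** Contents of monitoring reports lists "Data on the occurrence of events (according to the blinded group allocations" and gives adverse events on the same basis.
- **Action allowed.** Periodic monitoring lets the Central Research Ethics Committee, described there as a third party, recommend to the J-MISP director to "revise the study protocol or stop the study, if ethical problems, such as safety and efficacy issues, should arise".
- **Planned efficacy looks.** Interim analyses says "The analyses will be conducted twice during the study", with O'Brien-Fleming-type Lan-DeMets spending that holds the overall one-sided error at 2.5%. It gives a stopping rule for benefit at those looks only.
- **The management office's other work.** Under the case management section it holds case conferences, visits hospitals and meets case managers. Under Events, the site coordinator "will fax the event review sheet directly to the study group management office" when a serious adverse event occurs, sites may consult the office about unclear events, and it meets monthly with the chair of the event review committee to assess event details.
- **Other sections on periodic monitoring.** Both the section on protocol revision and Study termination mention periodic monitoring as a basis for action on safety issues.

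**The concern.** Two separate matters arise.

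**Access to the running comparison.** The management office supports the sites, advises them on unclear events and takes part in event review. If it also receives event totals by coded group and can work out which code is which, it knows the running difference in the primary endpoint. In an open trial that knowledge could affect effort at sites, how actively events are sought, and how borderline events are judged. It would also weaken the requirement, under Evaluation of events, that events be assessed with assignment blinded.

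**Efficacy looks outside the spending plan.** The quarterly remit covers efficacy but has no threshold and no link to the alpha spending. If it were used to stop for benefit, those looks would add to the two that the 2.5% was budgeted for.

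**Working it through.** **1. Can the codes be broken?** The office has a route to individual assignments, because case managers serve only the experimental group (Table 1). It also has details of individual events, from the faxed sheets and the monthly review. To identify a column it needs a quarter with few events, so the useful figure is the expected number of new events in each report.

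Inputs (Estimation of sample size): annual incidence 15% and 10.5%, 421 per group, 3.5 years' enrollment plus 1.5 years' follow-up, no loss to follow-up. Uniform accrual and exponential survival are my assumptions.

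Hazards: −ln(1−0.15) = 0.1625 and −ln(1−0.105) = 0.1109, so HR = 0.6826.

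The plan's own figure reproduces. Freedman's formula gives (1.960+1.282)² × [(1+0.6826)/(1−0.6826)]² = 295.2, rounded up to **296 events**, as stated. Schoenfeld's formula, 4(1.960+1.282)²/(ln 0.6826)², gives 289. (The same section also gives 518 per group, which these inputs do not reproduce. That is a separate matter, and 421 is used here.)

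Expected events by calendar year T, with a = min(T, 3.5), summed over both groups:

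E(T) = (421/3.5) × Σ { a − [e^(−λ(T−a)) − e^(−λT)]/λ }

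| Report | Cumulative events | New events |
|---|---|---|
| Month 3 | 1.0 | 1.0 |
| Month 6 | 4.0 | 3.0 |
| Month 9 | 8.9 | 4.9 |
| Month 12 | 15.7 | 6.8 |
| Month 60 | 295 | 18.7 |

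With one to five new events in a report, one known event in a known participant may be enough to tell the columns apart. If the labels stay fixed, later reports would then be readable too.

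**2. How many reports?** Follow-up from July 2006 through June 2011 is 60 months, and 60/3 = 20 reports. Counting to March 2011, the stated end of the study period, gives 57/3 = 19. Two efficacy looks are planned.

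**3. What could the extra looks do to alpha?** The plan states no threshold for the quarterly reports, so a range is shown. Method: simulated null Brownian path, with information at each quarter equal to E(T)/E(5). The planned looks are assumed at 1/3 and 2/3 information, since their timing is not stated. Their cumulative spend is 0.0001, 0.0060 and 0.025, and the bounds are about 3.70, 2.51 and 1.99. With only those looks, the error is 2.5%.

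| Threshold at each quarter (assumed) | 20 quarterly looks alone | With planned bounds included |
|---|---|---|
| Z>1.96 | about 16% (0.165) | about 16% (0.165) |
| Z>2.33 | about 8% | about 8.5% |
| Z>2.58 | about 4% (0.043) | about 5.5% |
| Z>3.00 | about 1.3% | about 3.3% |
| Z>3.29 | about 0.5% | about 2.8% |

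If the reports are used only to stop for harm or lack of effect, the one-sided error for benefit is not inflated.

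**4. The passages side by side.** Periodic monitoring allows a recommendation on safety and on efficacy. Interim analyses gives a rule for benefit at two looks only. The revision and termination sections connect periodic monitoring with safety. The first passage is therefore wider than the other three, and nothing reconciles them.

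**The case against.** **The tables may be pooled.** The wording could mean data shown with allocation masked. The text does not exclude this, but pooled counts would need no reference to group allocations, so coded columns are the more natural reading. If pooled data were meant, the fix only makes that explicit.

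**Codes may be hard to break.** On average a report adds about 296/20 ≈ 15 events, so one known event would seldom identify a column. Neither the table layout nor the labelling scheme is given, and the faxed sheet is not said to show the arm. This stands for later reports. It does not cover the first few, where step 1 expects far fewer events.

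**Safeguards exist.** Evaluators are blinded and do not act as case managers, and the event review committee assesses events with assignment blinded. These limit the harm. They do not cover the management office, which takes part in the monthly review.

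**Efficacy may mean lack of effect.** It is listed among ethical problems, the committee under this section only recommends, and termination passes through the steering committee. All of this is fair. It makes the extra looks possible, not certain.

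**Stronger readings that the document does not support.** A reader might infer that comparative results do leak, but the text shows only a route by which they could. A reader might infer that the true error rate is 16%, but that figure belongs to a Z>1.96 rule that the plan never states. A reader might also infer that the office proposes protocol revisions. The revision section gives that to the principal investigator, and the office only distributes the revised protocol.

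**Conclusion.** The point holds as a design weakness that is cheap to remove. The protocol itself fixes the frequency, content and recipients of the reports, so this is not detail left to another document. On the natural reading, the office running an open trial receives event totals by coded group, with labels that are weak protection when about 1, 3 and 5 new events are expected in the first three reports. Those counts rest on the design rates, uniform accrual and no loss to follow-up. The bias that could follow cannot be quantified from the document.

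The efficacy remit is inconsistent with the interim, revision and termination sections. Its effect on the one-sided 2.5% ranges from none (lack of effect only), through about 2.8% (Z>3.29 with planned bounds), to about 16% (Z>1.96). Every threshold in that range is an assumption. The concern about access to the comparison does not depend on these figures.

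**What to change.** 1. In Periodic monitoring and Contents of monitoring reports, send the study group management office event and adverse event counts pooled over both groups only.
2. Restrict by-group tables to the Central Research Ethics Committee as the independent body. The study progress control committee would then also receive the pooled version.
3. Reconcile Periodic monitoring with Interim analyses, protocol revision and Study termination: state that a recommendation to stop for benefit is made only at the two planned interim analyses, and that quarterly review of safety continues. If the efficacy wording was meant to cover lack of effect, say so.

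The cost is a second report template and a change of wording. The office loses a comparison that it does not need to run the trial, and the ethics committee's safety oversight is unchanged.

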### Revision of the study protocol and due process

The J-MISP director will immediately inform the ACTION-J principal investigator of the decisions of the central research ethics committee if the committee has recommended that the study protocol be revised due to the emergence of safety issues based on the interim analysis, periodic monitoring, serious adverse events, and/or other issues that might affect the conduct of the study. The ACTION-J principal investigator will call a meeting of the study group and discuss protocol revision based on the decisions of the central research ethics committee. If necessary, the principal investigator will propose the revised study protocol and submit it to the J-MISP director.

If the study evaluation committee and the central research ethics committee approve the revised protocol, the J-MISP director will adopt the revised protocol after deliberation in the steering committee. The study group management office will immediately distribute the revised protocol to all the on-site research staff through the on-site research coordinator. The on-site research coordinator will submit the revised study protocol to the on-site research ethics committee at each participating hospital.

The study is to be resumed after the revised protocol has been approved by each committee.

### Study termination

Based on the findings of the interim analyses, the Central Research Ethics Committee can make a recommendation to the J-MISP director to terminate the study. The committee can decide to terminate the study because of safety issues. This decision will be based on the findings of the interim analyses, the periodic monitoring, the occurrence of a serious adverse event, or other issues that possibly could affect continuation of the study. The principal investigator will promptly convene a meeting of the steering committee to consider whether this study should be terminated, according to the conclusion of the central research ethics committee. Then, if study termination is confirmed to be appropriate, the final decision will be made.

## Discussion

Suicide is a complex phenomenon that encompasses multiple factors. Ratios between 10 and 18 suicide attempts to 1 completed suicide have been estimated in other countries [25,26]. Although the ratio of suicide attempts to completed suicide is not known in Japan, many patients with self-injury from suicide attempts are transported to emergency departments in Japan [5].

In the absence of effective measures against suicide attempters, it has been difficult to reverse an increasing suicide trend in Japan. Case management by multi-sector collaboration is required.

The ACTION-J study is designed to evaluate the effectiveness of emergency facility-based case management for suicide prevention in 19 participating hospitals in Japan. ACTION-J is intended to provide valuable information on suicide attempters and to develop effective case management to reduce future risk for suicide attempters.
